## Methods/design

### Design

The CONSORT guidelines for evaluation of randomised controlled trials [45], the CONSORT extension for non-pharmacological treatment interventions [46], the SPIRIT checklist of protocol items and the TIDIER checklist for intervention description and replication [47] were adhered to in the design of this study and this protocol paper.

This study involves a two-arm randomised-controlled superiority trial with one intervention condition, guided mindfulness meditation, and one active-control condition, sham meditation. The design employed is a 2 (condition) X 2 (time) parallel-group design which is explanatory in nature. Measurement will take place at baseline (i.e. before randomisation, T1) and 6 weeks after baseline (T4). The delivery of the content of both the intervention condition and the active-control condition will take place between T1 and T4. Manipulation checks will be carried out to assess intervention acceptability, technology acceptance and meditation quality 2 weeks after baseline (T2) and 4 weeks after baseline (T3). See Table 2 for a description of the procedure.

**Table 2 Tab2:**
[figure not shown]
Timeline of Intervention

### Sample size (Incl. flow chart)

The statistical program G*Power was used to conduct power analysis in order to determine the appropriate sample size. Adhering to Cohen’s [48] guidelines for small (*r* = 0.1), medium (*r* = 0.3), and large (*r* = 0.5) effects, two-tailed alpha of .05 was assumed for all tests. With 2 groups, 6 measurements, an assumed correlation among repeated measures of 0.3 (typically low in such research; [49]) as well as a medium effect size (again typical in research on the cognitive effects of mindfulness; [10]) and a power of 0.8, the recommended sample size for mixed (repeated-measures and between factors) ANOVA was 56. As it is recommended that the sample size be a multiple of the number of measurements, a sample of at least 60 will be sought, 30 per group. Because of an anticipated attrition rate of 20 %, 38 participants are required per group i.e. 78 in total. Previous studies using Headspace have reported attrition rates between 20 and 40 % [41, 44]. We expect an attrition rate closer to 20 % because of the incentives in the form of course credit, lunches provided at data collection and free subscription to Headspace for 6 months following the intervention.

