**Method:**

The design employed is a randomised-controlled 2 (condition) X 2 (time) parallel-group design which is explanatory in nature. A sample of at least 60 participants will be recruited from the pool of students at NUI Galway, with those between the ages of 18 and 65 with an adequate level of English included. Participants will be randomly assigned following screening, using block randomisation with a fixed block of 6 and a 1:1 ratio, to either the mindfulness meditation group or a sham meditation group. Both groups will be given access to the Headspace app. This is an app which provides guided meditations to users. Participants in each group will receive unique codes granting access to either the experimental or active-control intervention materials. Group allocation will be double-blinded. The primary outcome measures will assess mindfulness, executive functioning, critical thinking, actively open-minded thinking and need for cognition. Secondary outcome measures will assess eudaimonic and hedonic wellbeing, positive and negative affect, and real-world outcomes. These will be measured at baseline and at the end of the intervention. Manipulation checks will assess adherence to the intervention, meditation quality and task difficulty and enjoyment.

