### Recruitment and randomisation

Students enrolled in psychology will be invited to participate and on acceptance of this invitation will fill out the screening questionnaire online. Those that satisfy the inclusion criteria will be selected to take part in the intervention and will be randomised to either the mindfulness meditation group or the sham meditation group with a 1:1 ratio. Block randomisation will be employed using a fixed block of 6 [50]. Unique Headspace access codes corresponding to the two conditions will be provided to the researcher. These will be labelled Condition A and Condition B and only after analysis will the nature of these conditions be revealed to the researchers by Headspace. Therefore both participants and researchers will be blinded. However, blinding can be readily undone on a participant-by-participant basis if necessary.

Potential participants will be invited to take part by email and through advertisements on social media. Announcements regarding the study will also be made by the researchers in lectures attended by 1st year and 2nd year undergraduate psychology students.

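### The recruitment target does not add up: 38 per group is 76, not 78, and the abstract gives the pre-attrition 60 as the number to recruit

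*Protocol article*

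**What the plan says.** In the protocol article, the Sample size section calculates 56 participants and rounds this up: "a sample of at least 60 will be sought, 30 per group". It then allows for 20% attrition and concludes that "38 participants are required per group i.e. 78 in total".

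The Method paragraph of the Abstract says: "A sample of at least 60 participants will be recruited from the pool of students at NUI Galway". It mentions no attrition allowance. The same paragraph describes allocation as "using block randomisation with a fixed block of 6 and a 1:1 ratio", and the Recruitment and randomisation section repeats the block size of 6.

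**The concern.** Two things do not fit.

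- **Per-group and total figures.** The total of 78 is presented as the same quantity as 38 per group. Under 1:1 allocation it is not, so one of the two printed figures must be wrong.
- **The meaning of 60.** In the sample size section, 60 is the number wanted once losses have occurred, because it is the number that is then inflated for attrition. In the abstract it is the number to be recruited.

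At stake is the point at which recruitment is complete. A trial that stopped at 60 would satisfy the abstract and still miss the number that the methods call required.

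**Working it through.** **Inputs from the Sample size section:** 2 groups, 6 measurements (m), correlation among repeated measures (rho) of 0.3, two-tailed alpha of 0.05, power of 0.8, calculated N of 56, 60 sought (30 per group), attrition of 20%. **From the Abstract and the Recruitment and randomisation section:** 1:1 allocation, fixed blocks of 6. **Assumption:** a medium effect means Cohen's f = 0.25. The text labels r = 0.3 as medium but gives no f.

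**1. Reproducing the 56.** For the between-groups test in a repeated-measures ANOVA, the noncentrality is f² × N × m / (1 + (m − 1) × rho), with 1 and N − 2 degrees of freedom.
- Per participant this is 0.0625 × 6 / (1 + 5 × 0.3) = 0.375 / 2.5 = 0.15.
- At N = 56 the noncentrality is 8.4 and power is 0.812, so 56 is reproduced.
- With f = 0.30 the same calculation gives N = 40. With f = 0.314, the equivalent of r = 0.3, it gives N = 36. Of these three values only 0.25 returns the protocol's figure.

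**2. Attrition allowance.** 30 / (1 − 0.20) = 37.5, rounded up to 38 per group. The 38 is reproduced.

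**3. The total.** 2 × 38 = 76. Other routes do not give 78 either: 60 / 0.8 = 75, and 60 × 1.2 = 72.

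**4. Fit with the blocks.**
- 78 / 6 = 13 complete blocks, so exactly 39 per group.
- 76 / 6 = 12.67. Twelve complete blocks give 36 per group. The remaining 4 come from an unfinished block and can split 1:3, 2:2 or 3:1, so 76 guarantees only 37 to 39 per group.

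**5. Participants with observed T4 data at 20% loss.**

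| Randomised | Remaining at 20% loss |
|---|---|
| 60 | 60 × 0.8 = 48 |
| 76 | 76 × 0.8 = 60.8 |
| 78 | 78 × 0.8 = 62.4 |

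**6. Power under the protocol's own calculation (f = 0.25).**

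| N | Noncentrality | Power |
|---|---|---|
| 48 | 7.2 | 0.748 |
| 56 | 8.4 | 0.812 |
| 60 | 9.0 | 0.839 |

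Reading the abstract's 60 as the number recruited therefore costs about 9 percentage points against 60 remaining (0.839 − 0.748 = 0.091), and takes power below the stated 0.80.

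**The case against.** The strongest reply is that little turns on this. Most of that reply stands.

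- The 76/78 slip is two participants in the safe direction, and either total leaves at least 60 at 20% loss. The 78 may be a deliberate rounding to whole blocks. The text does not say so, and 38 per group would then be the wrong figure.
- The abstract's 60 is a floor, so recruiting 76 or 78 does not breach it. Within the sample size section, the role of 60 is clear.
- A reader might infer that the trial will stop at 60. The documents do not support that. The methods state a higher requirement, and the Data collection section schedules three sessions of up to 30 each, a capacity of 90.
- The 48 are those with observed T4 data, not the analysed sample. The Statistical analysis section specifies intention to treat with baseline carried forward, so all 60 would be analysed. This does not restore the planned information, because a carried-forward baseline assigns zero change and adds no observed outcome. The protocol itself treats attrition as a reason to recruit more.
- A reader might also infer that the planned time-by-group test is severely underpowered. That does not follow from the recruitment count. With f = 0.25 applied directly to the 2 × 2 interaction and rho = 0.3, 48 participants give about 0.82. Much lower values need an effect definition that the protocol does not state.
- Attrition above 20% is already disclosed: the sample size section reports 20 to 40% in earlier studies of the app, and the Discussion names the risk to power.

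What the reply does not remove is that the printed per-group and total figures disagree, and that the abstract gives 60 a different meaning from the methods.

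**Conclusion.** The point holds as an inconsistency in the stated sample size. The per-group and total figures differ by two participants, with no effect on adequacy. The abstract's figure is 18 below the methods total (78 − 60). If it were followed literally, 48 would have observed T4 data at 20% attrition: 8 below the calculated 56 and 12 below the 60 sought. Power would be about 0.75 against the stated 0.80.

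The counts rest only on the protocol's own figures. The power figure also rests on f = 0.25 for a medium effect, on the six-measurement between-groups calculation that reproduces 56, and on counting only participants with observed T4 data. The shortfall is conditional on the abstract being followed over the methods, which the documents give no reason to expect.

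**What to change.** State one target in the abstract and in the sample size section: 78 randomised, 39 per group, in 13 complete blocks of 6, expected to leave about 62 with T4 data at 20% attrition. Replace 38 per group with 39, and label 60 (30 per group) in both places as the number wanted after attrition.

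The cost is wording only. The total of 78 is already printed and fits within the planned capacity of 90.

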### Sample characteristics

Competent university students over the age of 18 will be invited to participate. Though the study will be open to all students and advertised widely, it is anticipated that the majority of participants will be first and second year psychology students. First year and second year psychology students are awarded credit for participating in a variety of undergraduate final year research projects and postgraduate research projects. The sample will comprise University students at NUI Galway, over 18 years of age and below 65 years of age with English as first language or university level English (i.e. equivalent to 80 on TOEFL or 6.5 on IELTS; both standardised and recognised tests of English as a foreign language).

### Eligibility

Our inclusion criteria specify that University students at NUIG who are over 18 years of age, below 65 years of age and have either English as first language or university level English (i.e. equivalent to 80 on TOEFL or 6.5 on IELTS; both standardised and recognised tests of English as a foreign language) will be eligible for this study.

Those who are alcohol or drug dependent; are currently on any form of sedating medication, have suffered from any medical conditions associated with a head injury, spinal injury, epilepsy, or stroke (because these can interfere with cognitive performance) or do not possess normal or corrected-to-normal vision and hearing (required for computerised tasks) will be excluded. Furthermore those exhibiting clinical levels of depression, anxiety or psychotic symptoms (as assessed with the Modified Mini Screen) will be excluded. Debriefing phone calls will be made to those excluded and they will be offered access to the intervention materials. An experienced clinician has agreed to provide advice on the management of any participant in whom a high level of emotional distress is identified. Any such participants will also be provided with a database of relevant professionals and professional organisations.

### Recruitment and randomisation

Students enrolled in psychology will be invited to participate and on acceptance of this invitation will fill out the screening questionnaire online. Those that satisfy the inclusion criteria will be selected to take part in the intervention and will be randomised to either the mindfulness meditation group or the sham meditation group with a 1:1 ratio. Block randomisation will be employed using a fixed block of 6 [50]. Unique Headspace access codes corresponding to the two conditions will be provided to the researcher. These will be labelled Condition A and Condition B and only after analysis will the nature of these conditions be revealed to the researchers by Headspace. Therefore both participants and researchers will be blinded. However, blinding can be readily undone on a participant-by-participant basis if necessary.

Potential participants will be invited to take part by email and through advertisements on social media. Announcements regarding the study will also be made by the researchers in lectures attended by 1st year and 2nd year undergraduate psychology students.

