### Intervention

Intervention materials will be delivered via Headspace, a commercially available application which runs on all major smartphones, tablets and web browsers. The Headspace meditation scripts are designed by an individual with Buddhist monastic training who guides users through mindfulness meditations and key concepts related to mindfulness meditation using both audio and visual materials. In order to participate, individuals are required to have access to a smartphone or desktop computer with Internet access. Headspace makes meditating accessible by combining technology and simple techniques that are designed for new meditators. Participants can practice at any time of day wherever they prefer. Headspace offers straightforward, guided, bite-sized mindfulness training that is non-religious. We have signed guarantees with Headspace that participant data collected through Headspace will never be sold, distributed, or publicised (except anonymously in scientific publications with Headspace having no involvement in the conduct, analysis, or reporting of the research in any way).

Participants will be sent an email introducing Headspace and describing the sign-up process. To get started, participants are required to register on headspace.com using their name and email address. Each participant will be given a unique code providing free access to Headspace for the duration of the study. After registering, participants may begin meditating straight away.

The proposed intervention is 6-weeks in length. All participants will be encouraged to practice meditation/sham-meditation daily for the course of the 6-weeks by listening to each of the 30 ten-minute guided sessions which they will access through the Headspace app. The nature of the sessions they can access depends on the group they are assigned to.

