## Discussion

This study aims to investigate the claim that mindfulness practice facilitates critical thinking. It will also test whether executive function mediates the relationship between mindfulness and critical thinking in line with default interventionist theory, previous cross-sectional studies which examined this relationship, and previous experimental studies which suggested this relationship [12–17]. It will achieve this aim by randomising participants to either an experimental condition involving the learning of mindfulness meditation or an active-control condition involving guided sham meditations which will both be delivered through the same online application, Headspace. Dispositional mindfulness, executive function and critical thinking will be assessed at baseline and following the end of the intervention along with measures of intervention adherence, wellbeing, thinking dispositions and real-world outcomes of critical thinking. Manipulation checks assessing intervention acceptability and meditation quality will also be administered.

This study has many strengths. It is pre-registered with the ISRCTN registry which is openly accessible. The use of an active-control which is identical in expectations (which will be measured) and presentation (i.e. through the Headspace application and by [name], a trained Buddhist monk) represents an advance from the usual attention or waitlist controls employed in previous mindfulness meditation interventions [10]. Another advance is the use of objective measures of intervention adherence. Where most previous studies have relied on self-report measures of adherence (when included), the application used to deliver the intervention materials in this study will also track the amount of guided meditations participants engage in and for how long they engage with them. Finally, participants will be allocated to their respective groups without knowing which was the experimental condition and this information will also be kept from the primary researcher until after data analysis is complete in order to ensure a double-blind RCT design.

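### Shared Condition A / Condition B labels held by the researcher mean that learning one participant's arm reveals every allocation to that researcher, so single-participant unblinding is compatible with the promised researcher blind only if it bypasses the researchers

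*Protocol article*

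**What the plan says.** All but one of the relevant statements stand in one paragraph of the protocol article, under Recruitment and randomisation.

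- Who holds the codes: "Unique Headspace access codes corresponding to the two conditions will be provided to the researcher".
- How they are marked, and when the meaning is disclosed: "These will be labelled Condition A and Condition B and only after analysis will the nature of these conditions be revealed to the researchers". The app company is named as the party that discloses it.
- What is claimed to follow: "Therefore both participants and researchers will be blinded".
- The exception: "blinding can be readily undone on a participant-by-participant basis if necessary".

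The Discussion repeats the commitment as a strength of the design: "this information will also be kept from the primary researcher until after data analysis is complete".

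The same Recruitment paragraph fixes 1:1 allocation in blocks of 6. The Sample size section gives a planned total of 78.

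**The concern.** The codes are unique to each person, but each also carries one of two labels shared by the whole arm. A researcher with the list therefore knows who is grouped with whom from the start. Only the meaning of the two labels is hidden, and one fact about one person is enough to supply it.

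That fact could arrive in two ways. One is the formal unblinding that the article itself allows. The other is ordinary conversation. The Experimental condition section describes body scans and training in redirecting attention, while the Active-control section describes quiet sitting with occasional reminders to breathe. A participant who describes a session to a researcher, for example at the in-person sittings after the intervention, could give the arm away.

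At stake is the researchers' blind to all participants, possibly before outcomes are scored and analysed. The Halpern Critical Thinking Assessment (HCTA), a primary outcome, includes open-ended answers graded against prompts, so its scoring leaves some room for judgement. The double-blind design is also presented as one of the study's main strengths.

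**Working it through.** The article gives no figure on this point to reproduce. The check is a count.

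**Inputs.** Two labels, list held by the researcher, meaning withheld until after analysis; 1:1 allocation, fixed block of 6 (Recruitment and randomisation). Planned total N = 78 (Sample size). That section also gives 38 per group, which makes 2 × 38 = 76, and a minimum of 60. The mismatch between 76 and 78 is a separate matter and does not change the result, so all three totals are shown.

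**Step 1: the scheme as written.** Two labels and two arms allow 2 maps: A = mindfulness and B = sham, or the reverse. Learning the arm of one participant whose label is known rules out one map. One map remains, so the arm of everyone on the list follows. Known to that researcher after one disclosure: 78 of 78 (76 of 76; 60 of 60).

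**Step 2: the same disclosure with individual codes and no group label.** A 3:3 block of 6 has C(6,3) = 20 possible allocations. Once one member's arm is fixed, C(5,2) = 10 remain. For a researcher who knows the block boundaries, the probability that a given other member is in the same arm is 2/5 = 0.40, compared with 0.50 before. Outside the block nothing changes.

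| Total N | Shared labels: arms known | Individual codes: certain | Shifted from 0.50 to 0.40 | Still at 0.50 |
|---|---|---|---|---|
| 78 | 78 | 1 | 5 | 72 |
| 76 | 76 | 1 | 5 | 70 |
| 60 | 60 | 1 | 5 | 54 |

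**Step 3: the statements side by side.** Undoing the blind for one person, and keeping the meaning of the labels from the researchers until analysis is complete, can both hold only if the disclosed arm never reaches anyone with the labelled list. The article states no such condition and describes no such route.

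**The case against.** The strongest reply is that the article does not say unblinding passes through the researchers. The app company holds the key and each participant has a unique code. The company could therefore tell one participant, or the clinician who advises on distress, without informing the study team. That is correct. A reader might infer that participant-by-participant unblinding is impossible under this scheme, and the text does not support that. The route is merely undescribed, and a full protocol may describe it. The reply does not cover informal disclosure, where the information goes straight to a researcher.

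Four further inferences are tempting and should not be drawn.

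- *That one disclosure unblinds all participants.* It does not. Participants do not hold the list, and they stay blind.
- *That fixed blocks with visible labels make upcoming allocations foreseeable in a harmful way.* The labels are masked, and the Design section places baseline measurement before randomisation. No route to bias is shown, so this is no ground for asking for mixed block sizes.
- *That the people who hold the codes also grade the HCTA.* The article does not name the graders. Most other outcomes are self-report questionnaires or a computerised task, where a researcher's knowledge of the arm has little scope to change a score.
- *That the company's key-holding contradicts the statement about "Headspace having no involvement in the conduct, analysis, or reporting of the research in any way".* That phrase belongs to a guarantee on data use. It is at most a separate wording matter and adds nothing on blinding.

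**Conclusion.** The concern holds in a limited form. As described, the scheme does not protect the researcher blind that the article claims: one participant's arm, learned by a researcher who holds the labelled list, reveals all 78 planned allocations to that researcher. With unlabelled individual codes the same event would make 1 certain and leave 72 unchanged.

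This rests on two readings of the text: that the labelled list stays with a researcher involved in assessment or analysis, and that no unstated route keeps disclosures away from that person. It does not show that a disclosure will occur or that any outcome would be biased. It is a weakness in a stated safeguard that can be removed cheaply before the codes are issued.

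**What to change.** 1. Have the codes supplied one per sequence number, already in randomised order and with no group label. The researcher gives the next code to the next participant and does not see A or B.
2. Attach the masked A/B grouping to the data only after all outcomes are scored, including the open-ended HCTA answers, and the data are locked.
3. Keep a per-participant key with someone outside the assessment and analysis team, and state that any single unblinding goes through that person. One participant can then be unblinded without decoding the rest.

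**Cost.** The code list is reordered before supply, and no extra data are needed. The downside is that the code supplier, or another person outside the team, must hold the ordered list. If that is the app company, its part in allocation grows and should be stated openly; an independent colleague could hold the list instead.

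**Limit.** A researcher who has already heard one participant describe the sessions could still decode A and B once the grouping is attached. By then scoring and data lock are past, so only the analysis would be exposed.
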